#### Donor-recipient amino acid polymorphisms and physicochemical HLA incompatibility

Eplets are theoretically defined (combinations of) amino acids that have been subject to change, making clinical integration of this approach difficult [19–21]. Assessment of the physicochemical disparity between donor and recipient HLA, in addition to comparing the interlocus and intralocus amino acid polymorphisms in antibody-accessible regions of the HLA molecules may improve risk stratification and predict adverse outcomes post-transplant [22–24]. The specificity and stability of antigen-antibody binding is determined by the structural compatibility and the electrostatic and hydrophobic interactions between the two molecules [25]. Donor and recipient HLA class I and class II mismatches will be compared at the sequence level to derive the number and physicochemical disparity of amino acid polymorphisms on donor HLA molecules using the Cambridge HLA immunogenicity algorithm [22–24]. The solvent accessibility of these amino acid polymorphisms will also be assessed using the HLA Epitope Mismatch Algorithm (EMMA; https://hla-emma.com) and Cambridge HLA immunogenicity algorithm [24, 26]. The electrostatic dissimilarity between donor and recipient HLA molecules at the structural level will be assessed using the recently described electrostatic mismatch score (EMS-3D) [27]. These scores may provide additional predictive value for class I and II allo-antibody responses but the clinical applicability of one or more of these scores remains unclear [24, 27].

#### Quantifying the role of T-cell help in DSA development

Until recently, the contribution of T cells to DSA development was not quantifiable. T-cell help is essential in the development of immunoglobulin (Ig)-G DSA by promoting the differentiation and proliferation of antigen-specific naïve B cells into memory B-cells and plasma cells. Peptides derived from donor HLA molecules are presented by HLA class II molecules of recipient B cells to cognate helper T cells, which then provide signals and cytokines to these B cells to undergo affinity maturation, class switching and differentiation into plasma cells [28]. We will utilize the NetMHCIIpan software (www.cbs.dtu.dk/services/NetMHCII-2.3 and www.cbs.dtu.dk/services/NetMHCIIpan-3.2) [29] to determine the pan-specific binding of peptides to MHC class II alleles of known sequence using pre-specified affinity thresholds and peptide ranking and other approaches in development by the study team [22, 23, 30]. In addition, we will also utilize the predicted indirectly recognizable HLA epitopes (PIRCHE) computational algorithm, which is designed to predict indirectly recognizable HLA-derived donor peptides that may induce T-cell allorecognition and lead to the production of donor-specific anti-HLA IgG antibodies (https://www.pirche.com/pirche/#/features/bioinformatics) to quantify the “amount” of T- cell help [31]. A high number of PIRCHE, likely to represent a higher number of “theoretical” T-cell epitopes that can be presented by recipient HLA class II molecules, may correlate with clinical alloreactivity but the clinical significance of PIRCHE on long-term allograft outcomes is yet to be determined.

### Outcome measures

The primary outcome is the composite of de novo DSA (defined as mean fluorescence intensity [MFI] of over 500), or any biopsy-proven acute rejection or allograft loss (defined as returning to dialysis or death with functioning allograft) after parental donor kidney transplantation up to 60-months post-transplant. Secondary outcomes are individual components of the primary composite outcome (development of de novo DSA, any biopsy-proven acute rejection, allograft loss at 60-months post-transplant but also extended follow-up to 120-months post-transplant), acute or chronic AMR (including the presence of TG) or Chronic Allograft Damage Index (CADI) score of > 1 on allograft biopsy post-transplant, allograft function (creatinine-derived estimated glomerular filtration rate [eGFR] using the Chronic Kidney Disease-Epidemiology Collaboration [CKD-EPI] equation for recipients aged ≥16 years [32] or bedside Schwartz equation for recipients aged < 16 years [33–35]), and urine proteinuria.

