### Clinical and laboratory parameters

In addition to the immunological profiling and outcome measures, a number of donor and recipient characteristics will be extracted from registries, databases and local hospital healthcare records where appropriate and available. Data to be extracted include donor factors of age, sex, body mass index, donor relationship to recipient, comorbid conditions and race; recipient factors of age, sex, body mass index, race, socio-economic status (SES; derived from post-code in Australia or alternative SES parameters in other countries), prior episodes of non-adherence to immunosuppressive agents or missed appointments (as recorded in healthcare records), comorbid conditions (including complex syndrome, urological, liver or cardiac diseases) and dialysis duration; and transplant-related factors of transplant era, ischaemic time, sensitization status of percentage class I and II panel reactive antibody (%PRA), types and intra-patient variability of the calcineurin-inhibitor levels; all of which are known to be associated with the clinical outcomes of interest. Information relating to measures of potential sensitization to maternal antigens, including complications in maternal pregnancy including infections, breast-feeding and prior pregnancies will be sought from respective donors (where available).

Specific outcome measures include acute rejection (and Banff classification) at any time point post-transplant (types, severity and response to treatment), allograft function (creatinine and eGFR at 3 and 6 months, then annually post-transplant), allograft failure (including causes of allograft failure) and death (including causes of death) will be extracted from ANZDATA registry or relevant sources in other countries; and kidney biopsy reports, rejection-related treatment and response to treatment, intensity of immunosuppression (therapeutic drug levels for calcineurin inhibitor [CNI] at 3, 6, 12, 24, 36, 48, and 60 months post-transplant), proteinuria (urine protein/creatinine ratios at 3, 6, 12, 24, 36, 48, and 60 months post-transplant if available) and number/duration of all-cause and cause-specific hospitalisations will be extracted from local hospital and laboratory data. The data will be entered into a password-protected database (unique to each site) at least up to 5-years post-transplant (or until allograft loss up to 10-years post-transplantation using linkage data to ANZDATA and other country-specific registries).

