### Statistical analysis

Data will be presented as mean ± standard deviation (SD) or number (proportion) for continuous and categorical variables, respectively, with means and proportion compared using *t-test* and the chi-squared test where appropriate. We will develop models with different numbers of archetypes and choose which to use as the final model according to the residual sum of squares using the “elbow” method [47]. The archetypal models will assign scores based on a combination of pre-transplant immunological and clinical (donor, recipient and transplant) parameters to each recipient using the time from transplant to the composite primary outcomes of de novo DSA, any episodes of acute rejection and allograft loss; with the scores totalling 1. Each parameter will be assigned to a single archetype cluster on the basis of the highest archetype score (corresponding to “high immunogenic risk” profile, comprising of immunological risk factors). Additional models accounting for pre- and post-transplant factors (such as donor age, non-adherence) will also be constructed. A principal component analysis will be constructed to visualize the data matrix used as the input for the archetypal analysis. The principal component analyses will produce two main results: (i) a correlation circle, and (ii) a projection of the individuals. The correlation circle allows for a graphical examination of the relationships among the pre-transplant immunological and clinical parameters and the graphical parameter contribution of the axes (positive or negative contribution: vector direction; strength of the contribution: vector length when projected on the axis). We will identify distinct groups (i.e. archetypes), each comprising of a well-defined set of immunological and clinical parameters that may improve the risk stratification for “adverse immunological outcomes” for those accepting a parental donor kidney for transplantation, and separately for those who have received maternal or paternal donor kidneys. The Australian and New Zealand cohorts will be the derivation cohort for these archetypes, which will be validated in the cohorts from the United Kingdom and the Netherlands. We will next seek to build a predictive model (combined cohorts) to examine the associations between the archetype clusters and other pre-specified covariates and the primary outcome using univariate Cox proportional hazards regression models. A multivariable Cox model will be constructed by selecting covariates by Group Lasso and Doubly Robust Estimation (GLiDeR), a method of variable selection to identify confounders using an adaptive group lasso approach that simultaneously performs coefficient selection, regularisation, and estimation across the treatment and outcome models. Bootstrap resampling with replacement or subsampling without replacement will be used to investigate and quantify model stability. Separate models will be constructed for each of the secondary outcomes. The results of the model and covariates will be reviewed to ensure clinical relevance. Deviance and score residuals will be plotted to evaluate for poorly predicted individuals or individuals that may have had large influences on model parameters. The performance of the integrated prognostic model will be assessed by computing a non–time-specific area under the curve (AUC) using the measure of concordance from Somer’s Dxy statistic. For assessment of model calibration, patients will be risk-stratified on the basis of their predictive index, which is the linear combination of the product of the multivariate model β coefficients and their individual covariate values. Kaplan-Meier survival curves will then be plotted for patients who are stratified into quintiles of their predictive indices. The validation cohort’s AUC will be determined and predicted and observed mortalities will be compared. The association between archetypes and adverse outcomes will be examined in the prospective cohort, and to examine how the addition of other newly developed novel immunological assays will improve the test performance of the models.

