Additionally, this resource will further stimulate research interest in this and related areas leading to further improvements in kidney transplant and patient outcomes for this and other populations. Specifically, these include:The predictive value of novel assessment of donor/recipient gene compatibility for adverse allograft and patient outcomes such as acute rejection, allograft loss, recurrence of primary kidney disease and other complications occurring after kidney transplantation.The potential for individualizing immunological risk assessment to reduce adverse allograft outcomes in kidney transplant recipients.Establishment of an important resource that will comprise the largest cohort of pediatric and adolescent kidney transplant recipients worldwide, with the availability of high-resolution HLA typing (using the most advanced typing technique in NGS sequencing) and complete allograft and patient data. The improvement of outcome in this cohort of patients is critical because of their projected lifespan, burden of chronic disease and the likelihood that these recipients will require repeat transplantation and continuing long-term utilization of healthcare resources in the treatment of their disease burden.

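### Allograft loss counts every cause, the profiles built on it are described as immunological, and no stated analysis uses the causes of failure and death that are collected

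*Protocol article*

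**What the plan says.** Under Outcome measures, the third component of the primary composite is "allograft loss (defined as returning to dialysis or death with functioning allograft". No cause is excluded. The same component is a secondary outcome at 60 months, extended to 120 months, and no death-censored version is given.

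Under Statistical analysis, the archetypes are scored "using the time from transplant to the composite primary outcomes of de novo DSA, any episodes of acute rejection and allograft loss". The leading profile is described as "corresponding to “high immunogenic risk” profile, comprising of immunological risk factors", and the archetypes are said to be ones "that may improve the risk stratification for “adverse immunological outcomes” for those accepting a parental donor kidney for transplantation". The inputs are not HLA measures alone; they are "a combination of pre-transplant immunological and clinical (donor, recipient and transplant) parameters".

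Under Clinical and laboratory parameters, "allograft failure (including causes of allograft failure) and death (including causes of death) will be extracted from ANZDATA registry" or its equivalents in the other countries. Neither the outcome definition nor the Statistical analysis section returns to these causes.

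**The concern.** The study asks how immunological compatibility between parent and child affects the graft, and its Discussion intends the results to guide the choice of parental donor. A graft lost early to a technical failure, or a death unrelated to the graft, enters the composite on the same footing as a loss from rejection. Such events carry little information on compatibility and would weaken a real association. If they were also more common with one parent or one profile, for instance through a donor characteristic, a difference with a non-immune origin could be read as one of compatibility. The data needed to separate these cases are being collected, so leaving them unused has an avoidable cost.

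**Working it through.** **1. The passages side by side.** The definition is all-cause (Outcome measures), the interpretation is immunological (Statistical analysis), and the cause data exist (Clinical and laboratory parameters). No cause-specific, death-censored or competing-risk analysis is stated.

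**2. The plan's own figure.** Inputs from Sample size calculation: composite rate up to 40%, difference 0.10, two-sided 5%, power 80%, continuity correction, correlation 0.5, 4 observations, 10% missing, 479 pairs. The split between parents is not stated; I assume 0.40 against 0.30.
- Two proportions with continuity correction: 376 per group.
- Repeated-measures factor with m = 4, ρ = 0.5, q = 0.9: [mq + ρm(m−1)q²]/(mq)² = (3.6 + 4.86)/12.96 = 0.6528.
- Total: 2 × 376 × 0.6528 = 491, within 3% of 479. Close variants give 480 to 481.

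The figure is reproduced well enough to serve as a base. The point does not depend on it.

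**3. Dilution of the composite.** Assume the 0.40 against 0.30 contrast is wholly immunological, and that a fraction c of recipients otherwise free of an event, equal in both groups, have a non-immune loss or death by 60 months. Each risk becomes p + (1 − p)c, so the difference becomes 0.10 × (1 − c). The article gives no value for c; the range is mine.

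| c | Risks (%) | Difference (points) | Non-immune share of composite events | Power at 479 | Total on the 491 basis |
|---|---|---|---|---|---|
| 0 | 40.0 / 30.0 | 10.0 | 0 | 81% | 491 |
| 1% | 40.6 / 30.7 | 9.9 | 1.8% | 80% | 505 |
| 2% | 41.2 / 31.4 | 9.8 | 3.6% | 79% | 518 |
| 5% | 43.0 / 33.5 | 9.5 | 8.5% | 76% | 563 |
| 10% | 46.0 / 37.0 | 9.0 | 15.7% | 70% | 642 |

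Power is a repeated-measures approximation without continuity correction. A loss that follows a donor-specific antibody or a rejection changes nothing, because the composite has already occurred.

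**4. The separate graft-loss outcome.** Here no earlier antibody or rejection event hides a non-immune loss. The non-immune share of all losses cannot be smaller than the non-immune share of composite events: its numerator is at least as large and its denominator no larger. If a share s of reference-group losses is non-immune with hazard ratio 1, a cause-specific hazard ratio h is observed as h(1 − s) + s, so the excess h − 1 shrinks by the factor 1 − s. The article gives neither s nor h, so the size cannot be calculated.

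**5. When dilution becomes misattribution.** With the same immunological risk p in both groups but different non-immune fractions, the composite differs by (1 − p)(c_maternal − c_paternal). This is zero unless the non-immune losses differ by donor parent. The same reasoning applies to profiles.

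**6. Death with function by cohort.** Under Study recruitment and data capture, Australian and New Zealand pairs are approached only if the registry records them as living and resident there, and under Study procedure they attend a visit for blood sampling. A recipient who died with a working graft before recruitment cannot enter. Those cohorts derive the archetypes. For the United Kingdom and the Netherlands, which validate them, stored samples are used under a consent waiver and no such restriction is stated. One part of the outcome is therefore largely absent from derivation but may be present in validation.

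**The case against.** The strongest reply is that nothing here is an error. Counting death with function as graft loss avoids censoring at death and is a defensible primary component, and supporting analyses often sit in an analysis plan. The first part stands, and the primary outcome should stay. The second stands only in part: the protocol itself fixes both the all-cause definition and the immunological description, and the mismatch between them is on the page.

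Several stronger readings are tempting, and the document does not support them.
- *Non-immune losses are attributed to HLA profiles.* The aims in the Background speak of adverse allograft outcomes, the phrase about adverse immunological outcomes is never defined as the composite, and clinical factors enter both the archetypes and the Cox models.
- *A parental difference in graft loss could not be read immunologically at all.* De novo antibody, rejection, and antibody-mediated rejection or CADI score are secondary outcomes with their own models, where an immunological reading can be checked. Donor age and other clinical factors are collected.
- *The graft-loss hazard ratio falls from 1.6 to between 1.48 and 1.30.* This follows from the formula above for s of 20% to 50%. But the 60% in the Background is an upper figure for maternal against paternal donors, covers rejection as well as loss, and is not stated to be cause-specific. If it is already all-cause, diluting it again counts the effect twice.
- *Recurrent disease is plainly non-immune.* The Discussion lists "recurrence of primary kidney disease and other complications occurring after kidney transplantation" among outcomes for which gene compatibility may be predictive, so recurrence cannot simply be set aside.

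It is also fair to say that a death-censored version would change little within the Australian and New Zealand cohorts. Its value lies in comparison with the validation cohorts, and it would not remove the selection itself.

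**Conclusion.** The point holds in a limited form. The all-cause component does not match the immunological description of the profiles, and the causes collected are put to no stated use. The expected consequence is dilution: about 0.1 to 1.0 points of a 10-point difference in the composite for c of 1% to 10%. That rests on an assumed 0.40 against 0.30 split, a wholly immunological contrast, and non-immune losses equal in both groups. For the separate graft-loss outcome the dilution is larger, but its size is unknown. Misattribution is possible but conditional on a correlation that the article neither shows nor excludes. The unequal scope for death with function between derivation and validation cohorts is a further reason to separate that event. This is worth correcting; it does not invalidate the primary outcome.

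**What to change.** - Keep the all-cause composite as primary.
- Report the allograft-loss secondary outcome at 60 and 120 months both all-cause and death-censored, with death with function treated as a competing event.
- Add one supporting cause-specific analysis from the causes already extracted, with deaths and clearly non-immune losses as competing events. Handle unknown-cause losses and recurrent disease both ways, as sensitivity analyses.
- State that an association will be called immunological only if it is consistent in that analysis and in the separate antibody and rejection models.

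The cost is some extra analysis on data already planned for extraction. The drawbacks are fewer events in the cause-specific version and some error in the coding of causes, which is why it should support the primary analysis and not replace it.

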## Background

Kidney transplantation is the treatment of choice for people with kidney failure, conferring a significant survival advantage compared to people treated with long-term dialysis [1]. Live donor kidney transplantation is preferred because survival rates of patients and allografts are substantially longer in comparison with deceased donor transplants [2–4]. In addition, living donation facilitates pre-emptive transplantation, avoiding the deleterious effects on health, psychosocial and educational outcomes of dialysis treatment on children during critical periods of growth and development [3].

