Most pediatric and adolescent kidney transplant recipients require subsequent transplants and following allograft failure are often highly sensitized (with development of multiple anti-human leukocyte antigen [HLA] antibodies that may hinder future transplant potential) and at higher risk of death [5]. Selecting the donor kidney associated with the best possible long-term allograft outcome is vital. Parental donors account for over 60% of live donor kidneys for pediatric and adolescent patients with kidney failure in the United Kingdom, Australia and New Zealand [6, 7]. However, it is unclear whether maternal versus paternal donation is associated with differential allograft outcome. A recent population cohort study showed that kidney transplants from maternal donor kidneys were associated with an up to a 60% greater risk of acute rejection and allograft loss compared to paternal donor kidneys [8]. This finding is contradictory to the previously held paradigm that exposure to non-inherited maternal antigen (NIMA) may incite a lesser immunological response compared to exposure to non-inherited paternal antigen (NIPA). Previous cohort studies and experimental models have suggested that exposure of a child to the NIMA during pregnancy may lead to NIMA-specific tolerance. In one study, sibling transplants expressing NIMA were associated with lower risk of rejection and superior allograft outcomes compared to transplants expressing the NIPA [9–11]. Given that parental donors are the predominant source of live donor kidneys for pediatric and adolescent patients with kidney failure, this study will help inform whether HLA matching at the epitope, amino acid and physiochemical properties level may enhance the understanding of the differential antigenicity and immunogenicity of NIMA and NIPA on allograft outcomes following parental donor kidney transplantation. The findings from this study may potentially have important clinical implications in the selection of the appropriate parental donor kidney for transplantation.

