### Sample size calculation

The sample size calculation is based on the primary composite outcome of de novo DSA, any episodes of acute rejection and allograft loss. In our ANZDATA registry study comparing the allograft outcomes of maternal and paternal donor kidney transplants, a greater proportion of kidney transplant recipients who had received maternal donor kidneys experienced any rejection episode compared with recipients of kidneys from paternal donors (37 and 27%, respectively; *p* < 0.001) [4]. Data relating to the development of de novo DSA are not available from ANZDATA registry. Assuming that up to 40% of recipients may develop de novo DSA, acute rejection or lose their allografts within 60 months post-transplant, a sample size of 479 donor/recipient pairs (1:1 allocation to maternal and paternal door kidneys) will be required to achieve a power of 80% with a two-sided significance of 5% for detecting a difference of 0.10 between marginal proportions after applying continuity correction (and correlations score of 0.5 of at least 4 observations [for the composite outcome measures], and accounting for potential missingness of data of up to 10%) (Fig. 2). The expected recruitment of 520 parental donor/recipient pairs in the retrospective study should have adequate sample size and sufficient power to address the study question. Sample size calculation was determined using the expected time-averaged difference (TAD) between two means from continuous, correlated data using the GEE method in PASS Sample Size Software.

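### Allograft loss is defined only as return to dialysis or death with function, so a graft failure followed by re-transplantation without dialysis is not a loss event

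*Protocol article*

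**What the plan says.** The definition stands under Outcome measures: "allograft loss (defined as returning to dialysis or death with functioning allograft". It feeds two outcomes:

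- the primary composite, counted "after parental donor kidney transplantation up to 60-months post-transplant";
- the component analysed alone as a secondary outcome, "allograft loss at 60-months post-transplant but also extended follow-up to 120-months post-transplant".

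The Abstract, the study aims and the Sample size calculation use the term without redefining it. Clinical and laboratory parameters lists the registry data: "allograft failure (including causes of allograft failure) and death (including causes of death) will be extracted from ANZDATA registry" or equivalent sources in other countries. It does not define allograft failure there or say that it replaces the outcome definition, and its list does not name re-transplantation. The same section lets extended data capture run until allograft loss, up to ten years.

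The Background states that "living donation facilitates pre-emptive transplantation" and that "Most pediatric and adolescent kidney transplant recipients require subsequent transplants".

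**The concern.** A kidney graft can end in three ways: the recipient goes back to dialysis, dies with the graft working, or receives another kidney. The definition names the first two. The third overlaps with the first only if dialysis comes between failure and re-transplantation. The Background describes a population in which further transplants are usual and transplantation before dialysis is an advantage of living donation, so the uncovered route is foreseeable.

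This is more than a detail left to a fuller document. The article states a rule for a component of the primary outcome, and following that rule gives no event when the graft has in fact failed. Allograft loss analysed alone is most exposed, because no other component can pick the failure up. Extended data capture is also affected, since its end point uses the same term.

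**Working it through.** **1. The plan's own figure, for background.** The Sample size calculation gives 479 pairs from these inputs: "Assuming that up to 40% of recipients may develop de novo DSA, acute rejection or lose their allografts within 60 months post-transplant"; "detecting a difference of 0.10 between marginal proportions after applying continuity correction"; 80% power; two-sided 5%; four observations with correlation 0.5; up to 10% missing.

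- Comparing 0.40 with 0.30 needs 356 per group. With continuity correction, n/4 × (1 + √(1 + 4/(n × 0.10)))² = 376.
- The repeated-measures factor is [1 + (m − 1)ρ]/m. With m = 4 it is 2.5/4 = 0.625, giving 235 per group, 470 in total.
- With 10% of observations missing, m = 3.6 and the factor is 2.3/3.6 = 0.639, giving 241 per group, 482 in total.

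Both totals are within 3% of 479. The article does not say on which side of 0.40 the 0.10 difference lies; 0.30 is assumed here. The figure starts from an assumed 40% and not from the component definitions, so the present point leaves it unchanged.

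**2. Applying the definition.** Take a recipient whose parental graft fails at month t and who receives a second kidney without dialysis.

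- Returned to dialysis? No.
- Died with a functioning allograft? No.
- Does another section add re-transplantation? No.
- Is the registry failure item said to decide the outcome? No.

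The literal result is no loss event at month t. If the second graft later fails and dialysis starts, the wording could record a loss then, at the wrong date and for the wrong graft.

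**3. Size for allograft loss alone.** Let L be the true risk of loss and s the share of losses that go straight to re-transplantation. Missed events are L × s, which is a fraction s of all losses. The documents give neither value. Assume s = 5-20%, with L = 10% at 60 months and 20-25% at 120 months:

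- 60 months: 10% × 5% = 0.5 points, to 10% × 20% = 2 points.
- 120 months: 20% × 5% = 1 point, to 25% × 20% = 5 points.

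**4. Size for the 60-month composite.** Let u be the share of these recipients with no earlier de novo DSA or biopsy-proven rejection. Missed composite events are L × s × u. Assume L = 5-15%, s = 5-20% and u = 20-100%, applied to the expected 520 pairs:

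| L | s | u | Missed | Of 520 | Composite 0.40 becomes |
|---|---|---|---|---|---|
| 5% | 5% | 20% | 0.05 points | 0.3 | 0.3995 |
| 10% | 20% | 50% | 1.0 point | 5.2 | 0.390 |
| 15% | 20% | 100% | 3.0 points | 15.6 | 0.370 |

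Stretching s to 30% in the last row gives 4.5 points, 23.4 of 520, and 0.355. That row supposes that none of these grafts had shown DSA or rejection, which is an extreme case.

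**5. Maternal against paternal.** The observed difference in loss is L_M(1 − s_M) − L_P(1 − s_P), where M and P denote maternal and paternal donors. If s is equal in both groups, the absolute difference shrinks by the factor (1 − s) and the ratio is unchanged. If s differs, the error can go either way. The documents give no information on s_M or s_P.

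**The case against.** The strongest reply is that a short parenthesis in a condensed article need not be the full coding rule. Failure and its causes are taken from registries, and a graft replaced because it failed may well be recorded there. This stands in part: the data may exist, and analysts may use them sensibly. But the article gives an explicit definition and does not say that the registry item overrides it. Censoring at re-transplantation would not rescue the rule either, because the failure being censored is the event of interest.

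It is also fair that the Background statements show possibility and not frequency. The one on further transplants has no time frame. Its sentence adds that recipients are often highly sensitised after graft failure, which can hinder another transplant; that argues against quick, dialysis-free replacement being common. The one on pre-emptive transplantation concerns living donation in general. Both limits are accepted, and they are why the size is given only under assumptions.

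A reader might infer three stronger things that the documents do not support:

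- *Such recipients will certainly be analysed as having a surviving graft.* No handling rule for re-transplantation is given, so this is what the literal wording yields and not a stated plan.
- *Kidney function, antibody and rejection data from the second graft will be credited to the parental graft.* This is possible, but nothing says so. The primary outcome is tied to the parental transplant, and the De novo DSA section limits testing to antibodies against the maternal or paternal donor's HLA.
- *The comparison of mothers with fathers is biased in a known direction, for example because the other parent may be the second donor.* No part of the article speaks to this.

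**Conclusion.** The point holds for the definition itself. As written, graft failure followed by re-transplantation without dialysis produces no loss event, and no other section corrects that.

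Its weight falls on allograft loss as a separate secondary outcome at 60 and especially 120 months. There, every such failure is missed when it occurs: 5-20% of loss events if 5-20% of losses take this route. For the primary composite at 60 months the effect is probably small, since many failing grafts will already have counted through DSA or rejection. The illustrations above run from 0.05 to 3 points, or 4.5 points under the most extreme assumption. All these sizes rest on assumed loss risks and re-transplantation shares. Neither material bias in the primary outcome nor any direction of bias between maternal and paternal donors is shown. The change is still worth making, because it corrects a rule for a primary-outcome component at very little cost.

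**What to change.** Make three linked changes to the outcome definition and data collection:

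1. Under Outcome measures, define allograft loss as the earliest of return to dialysis, re-transplantation (including pre-emptive) or death with a functioning allograft, dated at that event.
2. End index-graft follow-up for eGFR, proteinuria, DSA and rejection at that date.
3. Under Clinical and laboratory parameters, add the re-transplantation date to the extracted items. State how the registry's allograft failure item maps to the definition in each country.

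The cost is a line of text and one extra extracted date per recipient. The article does not list that date, so its availability should be confirmed with each registry and not taken for granted. The sample size does not change.
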